### Ethical approval and registration

This study will be carried out in accordance with the standards of the International Committee on Harmonization on Good Clinical Practice and the revised version of the Declaration of Helsinki. The protocol of the trial has been approved by two ethics committees: the Institutional Review Boards (IRBs) of both the Oriental Hospital at Kyung Hee University Medical Center and the Kyung Hee University Hospital at Gangdong. The permission numbers are KOMCIRB 2011-28 for the Oriental Hospital at Kyung Hee University Medical Center and KHNMC-OH-IRB 2011-016 for the Kyung Hee University Hospital at Gangdong.

The process of obtaining consent will be carried out by the principle of informed consent, which consists of information, decisional capacity, and voluntarism. Prior to screening, written informed consent approved by the IRB will be obtained from all participants who present at a clinic in response to an advertisement. The investigator will explain the study by using non-scientific language before the subjects read the terms of consent. Subjects will be given adequate time to decide whether they wish to participate before signing the consent form. After this process, if the subject spontaneously wishes to participate in the study, they will sign the consent form.

This trial is registered with the ClinicalTrials.gov protocol registration system, ID NCT01579877.

## Discussion

This clinical trial, which will be conducted as one of the nationwide projects to provide scientific evidence for TKM, belongs to the 2011 Traditional Korean Medicine R&D projects funded by the Ministry for Health & Welfare & Family Affairs, Republic of Korea.

The present study emphasizes the significance of treatment for xerostomia in the elderly, which has been neglected clinically up to this point, and can play an important role in giving prominence to treatment for this condition. We anticipate that this study will reveal that a herbal prescription and a typical TKM treatment method, YMJ, can be an alternative treatment for xerostomia in the elderly, a condition that presently has no suitable remedy.

In general, herbal medicine is a key tool of TKM treatment and is known to have a great curative power for many diseases
[35,36]. YMJ, which is one of the most frequently used herbal formulas in Korea, is regarded to be safe and to have a beneficial effect on xerostomia in the elderly
[21]. However, to our knowledge, no randomized controlled trials have shown the effectiveness of YMJ for xerostomia. Therefore, the current study was designed to obtain objective clinical evidence on the effects and safety of YMJ for the treatment of xerostomia in the elderly. If the effects of YMJ are verified in the present study, it could be used as a new alternative treatment option by elderly individuals with xerostomia, which is highly prevalent and without established standard therapies in conventional medicine.

The current study has three potential strengths. First, it is unique because the subjects of this study will have general xerostomia without the structural damage to the salivary glands that occurs with autoimmune disease or a history of radiation. Second, the ‘*Yin-deficiency*’ questionnaire, an indigenous pattern identification tool in TKM, will be applied to diagnose the subjects’ xerostomia according to TKM theory. If a high correlation is found between xerostomia in the elderly and ‘*Yin-deficiency*’, this will provide reasonable evidence for prescribing YMJ for xerostomia in the elderly. Third, we will determine whether YMJ can change the subjective feeling of dry mouth as well as the salivary flow rate. Although the relationship between a subjective feeling of dry mouth and the salivary flow rate is controversial
[8,9,37], the change in these factors in association with YMJ treatment could be compared in this study.

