## Abstract

**Background:**

Xerostomia, a subjective sense of dry mouth, is not generally regarded a disease despite its high prevalence among the elderly, and therefore continues to impair affected patients’ quality of life. In traditional Korean medicine, ‘*Yin-Deficiency*’ has been implicated in the pathogenesis of xerostomia among the elderly. *Yukmijihwang-tang* is a famous herbal prescription used to relieve ‘*Yin-Deficiency*’, and reportedly has antioxidant effects; therefore, it is postulated that *Yukmijihwang-tang* can be used to treat xerostomia in the elderly. However, to our knowledge, no clinical trial has been conducted on the effects of *Yukmijihwang-tang* on xerostomia. Thus, we designed a randomized clinical trial to investigate the effects and safety of *Yukmijihwang-tang* on xerostomia in the elderly. In addition, we will clarify the aforementioned assumption that ‘*Yin-Deficiency*’ is the major cause of xerostomia in the elderly by identifying a correlation between xerostomia and ‘*Yin-Deficiency*’.

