## Methods/Design

### Objectives

The aims of this study are to:

(1) obtain clinical evidence regarding the safety and effects of YMJ in elderly individuals with xerostomia;

(2) identify a correlation between xerostomia in the elderly and the ‘*Yin-deficiency*’ state.

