### Inclusion and exclusion criteria

In general, the definition of elderly is used to describe people over the age of 60 years
[24]; in accordance, we will recruit subjects who are between 60 and 80 years of age and have experienced xerostomia for 3 months prior to participation. We have restricted the subjects’ ages to below 80 years because individuals over this age are considered to have lower eligibility in this study on the basis of the rationale that the incidence of disease is increased as an individual ages.Therefore, we set an upper limit of 80 years on the subjects’ ages by a consensus among geriatric disease specialists.

The subjects should present with VAS scores >4 for xerostomia 2 weeks before the study period. In addition, the unstimulated salivary flow rates of the subjects should be under 0.3 mL/min. The subjects must agree that they will not receive xerostomia-related treatments for 3 months after initiation of the study.

Subjects who report the following conditions will be excluded:

(1) a history of treatments for autoimmune diseases like Sjögren’s syndrome, rheumatism, or lupus;

(2) a history of craniocervical radiation therapy, organ transplantation, severe psychiatric illness, or major depression;

(3) the use of any other herbal prescriptions or nutritional supplements at the screening phase;

(4) the use of xerostomia-relieving medications (pilocarpine and cevimeline) or therapies for xerostomia (mouthwash, gum, and toothpaste for xerostomia).

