#### Statistical analysis

An independent statistician will perform a blind statistical analysis using SPSS 16.0 (SPSS Inc., Chicago, IL, USA). All data will be presented as means and SDs, and all analyses will be based on the intention-to-treat principle.

The analysis strategies in the present study are as follows.

First, we will use the ANCOVA to compare the changes in VAS scores (primary outcome) to evaluate the effects of YMJ and the placebo from the beginning (0 week) to the end (8 weeks) of the study period. Second, the secondary outcomes (DMSQ scores, USFR, SSFR, volume of residual saliva, salivary Ig A, chromogranin A, cortisol, and ‘*Yin-deficiency*’ score) will be analyzed in the same manner as the primary outcome. Finally, correlation between subjective (VAS and DMSQ) and objective xerostomia-related variables (USFR, SSFR, and residual saliva) will be analyzed by Pearson’s correlation coefficients. Also, we will find out how xerostomia-related variables correlate with ‘*Yin-deficiency*’ score or stress-related variables (salivary Ig A, chromogranin A, and cortisol), respectively, using Pearson’s correlation coefficients. In addition, we will check the AEs in YMJ and placebo group each and describe them using the descriptive statistics.

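### The planned correlation between Yin-deficiency score and dry mouth severity cannot show that Yin-deficiency is the major cause of xerostomia, nor support prescribing YMJ

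*Protocol article*

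**What the plan says.** All places are in the protocol article.

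- **Abstract, Background:** the trial is to clarify the assumption that Yin-deficiency "is the major cause of xerostomia in the elderly by identifying a correlation between xerostomia and" Yin-deficiency.
- **Objectives:** the second of two aims is to "identify a correlation between xerostomia in the elderly and the" Yin-deficiency state.
- **Discussion:** listed as a strength of the study is that, should the correlation be high, "this will provide reasonable evidence for prescribing YMJ for xerostomia in the elderly".
- **Sample size calculation:** the correlation aim is a pilot, uses the 96 subjects of the main comparison, and is to be reported descriptively.
- **Inclusion and exclusion criteria:** xerostomia for 3 months is required. "The subjects should present with VAS scores >4 for xerostomia 2 weeks before the study period", and "the unstimulated salivary flow rates of the subjects should be under 0.3 mL/min". No group without xerostomia is described.
- **Statistical analysis:** by Pearson coefficients, "we will find out how xerostomia-related variables correlate with" the Yin-deficiency score or the stress markers. The Yin-deficiency score is also a secondary outcome, and these "will be analyzed in the same manner as the primary outcome", that is, by ANCOVA.
- **Outcome measurement:** Yin-DQ1 has ten items, one of which is dry mouth or throat. It is completed at baseline and week 8. The VAS for xerostomia is compared between arms on the change from week 0 to week 8.

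**The concern.** The objective only asks for a correlation. The Abstract and the Discussion then attach two conclusions to it, one about cause and one about treatment. A correlation among people who all have the condition has no comparison group and no time order, so it cannot establish cause. Whether a treatment works, or works better in some patients, is a different question, and the randomised arms exist to answer it.

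At stake is the interpretation of one of the trial's two aims. If the Discussion is followed as written, a high coefficient would be presented as support for prescribing YMJ whatever the randomised comparison shows.

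**Working it through.** **1. Origin of n = 96.** The plan has no calculation of its own for the correlation. It takes over the total from the VAS comparison: 36 / (1 − 0.25) = 48 per group, 2 × 48 = 96. (Whether 36 follows from the stated effect and SD is a separate matter.)

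**2. Cause.** Set the entry criteria beside the Abstract. To link Yin-deficiency with *having* xerostomia, one needs people with and without it. All subjects here lie above a VAS cut-off and below a flow cut-off, so only the gradient of severity among patients can be estimated.

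**3. Prescribing.** The correlation and the YMJ effect are logically independent. A simulation illustrates this with 48 per arm, change SD 1.87 and the plan's effect of 1.54:

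| Yin-DQ1–VAS correlation | YMJ effect | Result |
|---|---|---|
| 0.6 | none | treatment significant in 5% |
| 0.6 | 1.54 in everyone | treatment significant in 98% |
| 0 | 1.54 in everyone | treatment significant in 98% |
| 0 | 1.54 on average, 1.2 more per SD of Yin-DQ1 | interaction significant in 85% |

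The same coefficient occurs with an inert and with an effective treatment. A zero coefficient is compatible with a treatment that works mainly in Yin-deficient patients.

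**4. Upward distortion from the shared item.** Suppose that of ten items with equal variance only the dry mouth item relates to the VAS, with correlation c, and that items correlate ρ with each other. Then r(VAS, total) = c / √(10 + 90ρ).

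- c = 0.6, ρ = 0.3: 0.6 / √37 = 0.10
- c = 1.0, ρ = 0: 1 / √10 = 0.32

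Both c and ρ are assumptions. The other nine items contribute nothing here, yet the total still correlates with the VAS.

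**5. Downward distortion from the cut-offs.** If selection keeps a fraction of the symptom distribution and reduces its variance to v, a population correlation R becomes R√v / √(1 − R² + R²v) under bivariate normality. The documents give no fraction, so 30% to 50% is assumed.

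- Top 30%: v = 0.265; R = 0.5 becomes 0.28, R = 0.3 becomes 0.16.
- Top 50%: v = 0.363; R = 0.5 becomes 0.33, R = 0.3 becomes 0.19.

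This assumes that the VAS reading used for selection is also the one correlated. The cut-off applies 2 weeks before the study period, and screening and baseline VAS are listed separately. If those two readings correlate 0.7 to 0.9 (assumed), R = 0.5 falls only to about 0.34 to 0.43. The flow cut-off is not modelled. Steps 4 and 5 pull in opposite directions, and the documents do not allow a net figure.

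**6. Precision of the correlation.** Fisher interval: tanh(atanh r ± 1.96 / √93).

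- r = 0.2: 0.00 to 0.39
- r = 0.3: 0.11 to 0.47
- r = 0.5: 0.33 to 0.64

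**7. Precision of an interaction.** With 2 × 36 = 72 evaluable, equal arms and a standardised Yin-DQ1, SE = 1 / √(72 × 0.25) = 0.236 residual SD. Detectable with 80% power: (1.96 + 0.84) × 0.236 = 0.66 SD of treatment effect per SD of Yin-DQ1, or 0.66 × 1.87 = 1.23 points in the units of the sample size section. For an interaction of 0.77 (half of 1.54), power is 42% with 72 and 52% with 96.

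**The case against.** The strongest defence is that the working parts of the plan are modest. The objective asks only for a correlation, Pearson coefficients supply it, and the Sample size section calls the aim a descriptive pilot. The Discussion sentence is conditional. Just before it, the same section ties use of YMJ to its effects being verified in the trial. All of this stands, and it limits the point to two inferences. It does not rescue them, because the caution of the Sample size section is not carried into the Abstract or the Discussion sentence.

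Four stronger readings are tempting but not supported:

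- *That the correlation is meant to settle the matter.* The documents speak of clarifying an assumption and of reasonable evidence, which is weaker.
- *That a weak correlation would be held against the theory.* The documents discuss only a positive result.
- *That the trial already collects what both questions need.* This is true only of the prescribing question, where baseline Yin-DQ1 and the VAS change exist in both arms. The cause question needs people without xerostomia.
- *That the absence of an interaction test is an error.* No objective or hypothesis claims that YMJ works better in Yin-deficient subjects, and a condensed article may leave an exploratory model to the analysis plan.

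**Conclusion.** The point holds for the two inferences and no further. The planned correlation describes severity among patients. It cannot show that Yin-deficiency is the major cause of xerostomia in the elderly, and a high value is no evidence for prescribing YMJ. This conclusion rests on the entry criteria and the stated analysis, and needs no numerical assumption.

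The figures are secondary. The shared-item artefact (0.10 to 0.32) and the attenuation (0.5 to somewhere between 0.28 and 0.43) rest on assumed item correlations, selection fractions and screening–baseline correlation. They are illustrative, and a reader should not conclude that the coefficient is biased in a known direction.

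The change should be made because it governs what one of two aims may conclude. Eligibility, the primary endpoint, the randomised comparison and the sample size are untouched.

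**What to change.** 1. Restate the second aim as the association between Yin-DQ1 and symptom severity among elderly subjects with xerostomia at baseline, reported with a 95% CI.
2. Repeat it with a nine-item Yin-DQ1 score that omits the dry mouth item, and report both.
3. Delete the major-cause inference from the Abstract and the prescribing inference from the Discussion. Rest any statement on use of YMJ on the randomised treatment effect alone.
4. Optionally, add baseline nine-item Yin-DQ1 and its interaction with arm to the VAS ANCOVA, labelled exploratory and reported with a CI. Given its low power, it should not carry a prescribing statement.

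The cost of items 1 to 3 is wording and one extra coefficient; item 4 adds two model terms. No new data are needed. The cause question stays open: it would need a different sample that includes elderly people without xerostomia, ideally followed over time.

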## Trial status

This study is currently recruiting patients.

## Abbreviations

AE: Adverse event; CRA: Clinical research associate; CRC: Clinical research coordinator; CRF: Case report form; CRO: Contract research organization; DMSQ: Dry mouth symptom questionnaire; Ig A: Immunoglobulin A; IRB: Institutional review board; QoL: Quality of life; SAE: Serious adverse event; SSFR: Stimulated salivary flow rate; TKM: Traditional Korean medicine; USFR: Unstimulated salivary flow rate; VAS: Visual analogue scale; YMJ: *Yukmijihwang-tang.*
